**Table 6. Lapatinib Starting Dose and Dose Reduction Schedule**

| Starting dose | 1500 mg/day | *** Patients requiring a third dose reduction should be taken off study unless in the opinion of the investigator & GSK Medical Monitor, there is reason to believe that the patient is still experiencing clinical benefit |
| --- | --- | --- |
| First dose reduction | 1250 mg/day |

* if no recovery after 3 weeks of holding drug, patients should go off study unless in the opinion of the investigator & GSK Medical Monitor, there is reason to believe that the

patient is still experiencing clinical benefit.

**Table 7**. Dose Reduction Criteria and Guidelines for Management of lapatinib Associated Toxicity

|  | Grade | **Guideline for management** | **lapatinib dosage modification*** |
| --- | --- | --- | --- |
| Diarrhea | 1 | No intervention | None |
| 2 | Loperamide (4 mg at first onset,  followed by 2 mg every 2–4 hrs  until diarrhea free for 12 hrs) | None; If unacceptable to patient or medically concerning then hold until recovery  to < grade 1, up to 21 days*. Restart at same dose**. |
| > 3 (*despite optimal*  *use of loperamide)* | Hold until recovery to < grade 1, up to 21 days*. And then reduce 1 dose level. |
| Rash | 1 | No intervention | None |
| 2 | Any of the following:  minocycline+, topical  tetracycline or clindamycin,  topical silver sulfadiazine,  diphenhydramine,  oral prednisone (short course) | None; If unacceptable to patient or medically concerning then hold until recovery  to < grade 1, up to 21 days*. Restart at same dose**. |
| > 3 | Hold until recovery to < grade 1, up to 21 days*. And then reduce 1 dose level. |
| Other  Toxicity **(excluding**  **left ventricular**  **dysfunction and**  **pneumonitis,**  **see below)** | 1 | No Intervention | None |
| 2 | Treatment as appropriate | None; If unacceptable to patient or medically concerning then hold until  recovery to < grade 1, up to 21 days*. Restart at same dose **. |
| 2 prolonged or  clinically significant  and grade > 3 | Treatment as appropriate | Hold until recovery to < grade 1, up to 21 days and then reduce 1 dose level* |
| * if no recovery after 3 weeks of holding drug, patients should go off study unless in the opinion of the investigator & GSK Medical Monitor, there is reason to believe that the patient is still experiencing clinical benefit.  ** if dose has been previously held for grade 2 toxicity and grade 2 symptoms recur, OR if the patient finds the symptoms unacceptable, hold dose until recovery to < grade 1 and then reduce dose one level  + recommended dose: 200mg po bid (loading dose), followed by 100mg po bid for 7-10 days | | | |

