**3.6 Dosing delays/dose modifications**

Starting dose and dose modifications for unacceptable toxicity are listed in Table 6. For toxicity that is thought to be related to lapatinib, the daily dose of lapatinib will be decreased according to the schedule displayed in the Table 7.

Dose adjustments are to be made according to the greatest degree of toxicity. Toxicities will be graded using NCI Common Terminology Criteria for Adverse Events (CTCAE) version 3.0.

The most common toxic effects of lapatinib are:

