**3.6.1 Dose Delays and Dose Reductions**

Treatment may be delayed, up to 2 weeks, to allow for resolution of toxicity except in the event of NCI CTCAE Grade 3 or 4 left ventricular cardiac dysfunction or NCI CTCAE Grade 3 or 4 interstitial pneumonitis. The Investigator must consult the GSK Medical Monitor prior to continuing therapy for any subject requiring a delay of more than 2 weeks for unresolved toxicity, but in general, such subjects should be withdrawn from the study. If treatment is delayed for reasons other than toxicity (i.e., unplanned travel or vacation, or lack of transportation to the site) and the subject has insufficient investigational product available, the subject should resume the usual dosing schedule once drug supply has been made available. However, if the subject has been off therapy for more than 2 weeks, the Investigator must consult the GSK Medical Monitor prior to continuing therapy.

Dose reduction for drug-related toxicity is permitted; however the GSK Medical Monitor must be consulted prior to implementing any change in dosing. Only one dose reduction is permitted per subject and subjects should not be rechallenged to a higher dose level. If a NCI CTCAE Grade 3 or 4 drug-related event (other than left ventricular cardiac dysfunction or interstitial pneumonitis) has occurred, the investigator may discuss with the GSK Medical Monitor whether a reduction of dose is appropriate.

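### For grade 2 toxicity that the patient finds unacceptable, Table 7 says to restart at the same dose and its own footnote says to reduce; the neighbouring dose-reduction rules also need reconciling

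*Protocol*

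**What the plan says.** Table 7 of the protocol has three blocks: diarrhoea, rash and other toxicity. In each, the grade 2 dosage cell reads "None; If unacceptable to patient or medically concerning then hold until recovery" and, after the hold, "Restart at same dose", with a double-asterisk pointer to a footnote. That footnote gives two triggers for a reduction. The first is "if dose has been previously held for grade 2 toxicity and grade 2 symptoms recur". The second follows directly: "OR if the patient finds the symptoms unacceptable, hold dose until recovery to < grade 1 and then reduce dose one level".

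For the highest-grade diarrhoea and rash rows, Table 7 reads "Hold until recovery to < grade 1, up to 21 days*. And then reduce 1 dose level"; the matching row for other toxicity also ends in a one-level reduction. Section 3.6 ties the dose to this table for toxicity thought to be related to lapatinib: "the daily dose of lapatinib will be decreased according to the schedule displayed in the Table 7". Section 3.6.1 words grade 3 or 4 drug-related events (left ventricular dysfunction and interstitial pneumonitis aside) differently: "the investigator may discuss with the GSK Medical Monitor whether a reduction of dose is appropriate".

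Two other places bear on the same decisions. The diarrhoea guidelines in section 3.5.3 say that a reduction should be considered at grade 2, in discussion with the medical monitor. On the number of reductions, section 3.6.1 allows one per subject and no return to a higher level. Table 6 lists one reduced level, 1250 mg/day, but its note deals with patients who need a third reduction.

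**The concern.** A dose-modification table has to give the treating physician one answer per event. Here the trigger that depends on the patient's own judgement of grade 2 symptoms has two answers within one table: full dose by the cell, reduced dose by the footnote. It applies in all three toxicity blocks, including diarrhoea and rash, the two most frequent related events at 1500 mg/day in Table 3.

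At stake is how individual patients are dosed and how their toxicity is managed. Two patients with the same event could be handled differently because their physicians relied on different lines. The grade 3-4 text, the grade 2 diarrhoea guidance and the count of permitted reductions add to the uncertainty. Safety is a secondary outcome of the trial, so its description depends on the rule that was applied.

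**Working it through.** The plan gives no figure to reproduce on this point. The main check sets the instructions side by side for a patient on the starting dose of 1500 mg/day, with 1250 mg/day as the first reduced level (Table 6).

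| Event | Source | Instruction | Resulting dose |
|---|---|---|---|
| Grade 2, unacceptable to the patient, first hold | Table 7 cell | hold, then same dose | 1500 mg/day |
| The same | Table 7 double-asterisk footnote | hold, then one level down | 1250 mg/day |
| Grade 3-4, drug-related | Table 7 with section 3.6 | hold, then one level down | 1250 mg/day |
| The same | Section 3.6.1 | reduction may be discussed | 1500 or 1250 mg/day |
| Grade 2 diarrhoea | Section 3.5.3 | consider a reduction | 1500 or 1250 mg/day |
| Number of reductions | Section 3.6.1 | one | not applicable |
| The same | Table 6 note | refers to a third | not applicable |

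**Grade 2.** The conflict is confined to the patient-unacceptability trigger. A medically concerning event appears only in the cell, and recurrence after an earlier hold appears only in the footnote, so neither of those has two answers. The comma and the capitalised OR in the footnote make unacceptability a trigger in its own right, separate from recurrence.

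**Grade 3-4.** One side directs a reduction and the other leaves it to discussion. The same event can therefore be handled in two ways, but need not be. The signs printed as greater-than 3 may be greater-or-equal signs lost when the text was read from the PDF. If they are literal, the diarrhoea and rash rows cover grade 4 only, and the tension remains for grade 4.

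**Size of the grade 2 conflict.**

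- From Table 3, related events at 1500 mg/day: diarrhoea 147/273 = 54%, rash 89/273 = 33%.
- Planned sample size: 20. Expected patients: 20 × 0.54 = 10.8 with diarrhoea and 20 × 0.33 = 6.6 with rash.
- Assumed, because the protocol does not give them: 20% to 40% of these are grade 2, and 25% to 50% of those are unacceptable to the patient.
- Diarrhoea: 10.8 × 0.20 × 0.25 = 0.54, up to 10.8 × 0.40 × 0.50 = 2.16 patients.
- Rash: 6.6 × 0.20 × 0.25 = 0.33, up to 6.6 × 0.40 × 0.50 = 1.32 patients.
- If no patient had both, the sum would be 0.87 to 3.48; overlap lowers it. Other toxicity is not counted.
- Dose difference: (1500 − 1250)/1500 = 16.7%.

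**The case against.** The strongest reply is that the footnote hangs on the same-dose instruction, so it qualifies that instruction and does not compete with it. Two readings would then give one answer each. In the first, the opening condition of an earlier hold governs both limbs, so a first hold returns to the same dose and a later one leads to a reduction. The punctuation and the capitalised OR tell against this. In the second, the footnote is an exception: medically concerning events restart at the same dose and patient-unacceptable ones are reduced. That cancels the first trigger that the cell itself names. Either way the wording needs repair, so the objection does not remove the grade 2 point.

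For grade 3-4 events the reply has more force. Table 7 is presented as guidelines, section 3.6.1 requires the medical monitor to be consulted before any dosing change, and section 3.5.3 likewise says to hold lapatinib for grade 3-4 diarrhoea and discuss it. The diarrhoea row also applies only when loperamide has been used optimally. Section 3.6.1 nowhere directs a restart at full dose. This is why the grade 3-4 point is secondary. It is not empty, because section 3.6 says without qualification that the dose follows Table 7.

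A reader might also see a contradiction in the other-toxicity block, where a medically concerning grade 2 event restarts at the same dose and a prolonged or clinically significant one is reduced. Those terms are undefined, and the lower row can be read as a step up in severity. That is vague wording, not a demonstrated conflict, and it forms no part of this point.

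**Conclusion.** The grade 2 conflict stands as an internal contradiction: one trigger, two doses, in all three blocks of Table 7. The grade 3-4 mismatch, the separate wording for grade 2 diarrhoea and the disagreement over the number of reductions are real but secondary. The grade 2 conflict could reach perhaps a few of the 20 patients, with a dose difference of 16.7%. That count rests on the assumed grade 2 and unacceptability shares. The contradiction itself needs no assumption.

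Two stronger conclusions are tempting and are not supported. One is that the CTC result would blend two exposure policies. Nothing in the protocol shows that this dose difference in a few patients would move it, and section 1.3.4 describes absorption as highly variable. The other is that a reduction made on one reading could never be undone and would use up all remaining room. Section 3.6.1 alone suggests this, but the Table 6 note on a third reduction leaves the number of permitted steps unsettled.

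The issue is one of patient-level dosing and safety management, and should be corrected on that ground.

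**What to change.** Reconcile four pairs of passages so that each trigger has one stated consequence:

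- the three grade 2 cells of Table 7 with the double-asterisk footnote;
- the grade 3-4 sentence of section 3.6.1 with Table 7 and section 3.6;
- the grade 2 diarrhoea guidance in section 3.5.3 with Table 7;
- the Table 6 note with the limit on reductions in section 3.6.1.

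Which consequence applies in each case is for the sponsor's clinicians, and no view on it is given here. The cost is one wording amendment, with no change to sample size, visits or assessments.

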**4. REGULATORY AND REPORTING REQUIREMENTS**

It is the responsibility of the investigator to document all adverse events which occur during the investigation. An adverse event is any untoward medical occurrence in a patient or clinical investigation subject, temporally associated with the use of the medicinal product, whether or not considered related to the medicinal product. *An AE can therefore be any unfavorable and unintended sign (including an abnormal laboratory finding), symptom, or disease (new or exacerbated) temporally associated with the use of a medicinal product.* Anticipated day-to-day fluctuations of the disease under study that do not represent a clinically significant exacerbation or worsening need not be considered an adverse event.

All adverse events occurring from the first dose of investigational product until five days after the last dose must be recorded **regardless of whether or not they are considered drug related.** In addition, any SAEs which occur as a result of protocol specific diagnostic procedures or interventions must also be reported.

**The sponsor is responsible under ICH GCP for reporting all safety events and information to the regulatory authorities and relevant ethics committee as required within the given reporting timelines.**

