a Pre-menopausal women of child-bearing potential must have a negative urine or serum pregnancy test within 7 days before Day 1 of treatment, In the event of suspected pregnancy during the study, the test should be repeated.

b Laboratory/vital signs abnormalities should not be reported as adverse events (AEs) unless any criterion for a serious adverse event (SAE) is fulfilled, or laboratory/vital signs abnormality causes the subject to discontinue from the study, or the investigator insists the abnormality should be reported as an adverse event.

c In the event of any new or worsening respiratory symptoms (e.g. cough, breathlessness), appropriate medical advice should be sought promptly. Any symptoms should be treated as clinically indicated and reported as an AE or SAE if appropriate.

d Any ongoing study-related toxicity or SAE at discontinuation must be monitored until resolution.

e After discontinuation from treatment, subjects must be followed up for all existing and new AEs for 30 calendar days after the last dose of study drug. All new AEs occurring during that period must be recorded (if SAEs, they must be reported within 24 hours) and followed to resolution where possible.

f After discontinuation from the study for any reason, where possible subject, subject’s family, or the subject’s current physician must be contacted every 8 weeks for survival information until death.

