#### 3.3.3.2 Procedures for discontinuation

#### Subjects who discontinue should, if possible, be seen and assessed by an investigator(s). The reason for discontinuation and the date of discontinuation must be documented on the case report form (CRF). If possible any diary cards, questionnaires (e.g. for Quality of Life assessments) and investigational products should be returned by the subject.

All subjects who have new or worsening CTC grade 3 or 4 laboratory values at the time of discontinuation must have further tests performed and the results recorded on the appropriate CRF until the laboratory values have returned to CTC grade 1 or 2, unless these values are not likely to improve because of the underlying disease. In these cases, the investigators must record their opinions on the CRFs and in the subject’s medical records. Laboratory abnormalities should not be reported as adverse events unless any criterion for an SAE is fulfilled, the laboratory abnormality causes the subject to discontinue from the study, or the investigator insists the abnormality should be reported as an AE.

At discontinuation all on-going study-related toxicities and SAEs must be followed until resolution, unless in the investigator’s opinion, the condition is unlikely to resolve due to the subject’s underlying disease.

After discontinuation from treatment, subjects must be followed up for all existing and new AEs for 30 calendar days after the last dose of study drug. All new AEs occurring during that period must be recorded (if SAEs they must be reported within 24 hours) and followed up for resolution as above.

Any subject who withdraws from study treatment for reasons other than progression should continue, where possible, to have objective tumour assessments every 8 weeks in order to collect information on progression of disease.

When disease progression has been documented, the long-term follow up information for survival should be collected at least every 8 weeks by telephone contact with the subject, subject’s family, or by contact with the subject’s current physician.

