### 4.3 Definition of Serious Adverse Events

A serious adverse experience is any event which is fatal, life threatening, disabling or incapacitating or results in hospitalization, prolongs a hospital stay or is associated with congenital abnormality. In addition, any experience which the investigator regards as serious or which would suggest any significant hazard, contraindication, side effect or precaution that may be associated with the use of the drug should be reported as a serious adverse event. Examples of such events are invasive or malignant cancers, intensive treatment in an emergency room or at home for allergic bronchospasm, blood dyscrasias or convulsions that do not result in hospitalization, or development of drug dependency or drug abuse.

Abnormal laboratory findings (e.g., clinical chemistry, hematology) or other abnormal

assessments (e.g., x-rays, scans, vital signs, etc.) that are judged by the investigator as

**clinically significant** will be recorded as AEs or SAEs if they meet the definition of an

AE or SAE.

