### 4.4 Reporting Serious Adverse Events

Any serious adverse events which occur during the clinical study or within 30 days of receiving the last dose of study medication, whether or not related to the study drug, must be reported by the investigator. In addition, any SAEs which occur as a result of protocol specific diagnostic procedures or interventions must also be reported.

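### Adverse-event recording ends five days after the last dose in section 4 but 30 days after it in section 3.3.3.2 and Table 5, and two default rules apply to non-serious laboratory abnormalities

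*Protocol*

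**What the plan says.** **Recording window.** Section 4 of the protocol sets the period for all adverse events, related or not: "All adverse events occurring from the first dose of investigational product until five days after the last dose must be recorded". Section 3.3.3.2, on discontinuation, says that after treatment ends "subjects must be followed up for all existing and new AEs for 30 calendar days after the last dose of study drug". Table 5 footnote e gives the same 30 days. Both places add: "All new AEs occurring during that period must be recorded". For serious events, section 4.4 requires the investigator to report "Any serious adverse events which occur during the clinical study or within 30 days of receiving the last dose of study medication".

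**Laboratory findings.** The general definition in section 4 allows an abnormal laboratory finding to be an adverse event. Section 4.3 says that abnormal findings which the investigator judges clinically significant "will be recorded as AEs or SAEs if they meet the definition of an" AE or SAE. Section 3.3.3.2 says the opposite by default: "Laboratory abnormalities should not be reported as adverse events unless any criterion for an SAE is fulfilled". It allows two further exceptions: the abnormality makes the patient leave the study, or the investigator insists on reporting it. Table 5 footnote b repeats this rule and extends it to vital signs. Section 4.3.4 makes every Grade 4 laboratory abnormality an SAE.

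**Role of the data.** The synopsis and section 2.2 name the safety of lapatinib in this population as one of two secondary outcomes.

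**The concern.** The adverse-event data are the raw material of a stated secondary outcome, and two sets of instructions govern what enters them. An investigator who consults section 4, the natural place to look for reporting rules, may stop collecting non-serious events on day 5. One who works from Table 5 or section 3.3.3.2 continues to day 30. Similarly, a non-serious laboratory abnormality judged clinically significant is to be recorded under section 4.3 but is left out by default under footnote b.

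The incidence reported would then depend partly on which page was followed, and could vary from patient to patient. With 20 planned patients, one patient more or fewer with a given event moves its incidence by 1/20 = 5 percentage points. An analysis plan cannot repair this, because it cannot tabulate events that were never recorded.

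**Working it through.** The protocol gives no figure to reproduce. The check compares the texts and scales the gap.

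**1. Do the two windows really conflict?** They might not if section 4 governed recording and section 3.3.3.2 only follow-up of events already known. That reading fails: section 3.3.3.2 and footnote e cover new as well as existing events and require the new ones to be recorded. All three texts are current, and none gives way to another. The five days cannot be dismissed as a plain slip either, since section 4.5 uses the same period for pregnancy notification.

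**2. Which events are affected?**

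| Event after the last dose | Section 4 | 3.3.3.2 and footnote e | 4.4 |
|---|---|---|---|
| Non-serious, onset days 0 to 5 | recorded | recorded | not covered |
| Non-serious, onset days 6 to 30 | not required | recorded | not covered |
| Serious, to day 30 | required only to day 5 | recorded | reported |

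Section 4.4 settles the serious events. What remains is non-serious events with onset on days 6 to 30.

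**3. Size of the gap.** Inputs: 5 days (section 4), 30 days (section 3.3.3.2 and footnote e) and 20 patients (synopsis). Treatment duration is not fixed by the protocol. For illustration, take 28 days (the one-month minimum, with a visit at week 4) and 168 days (the last visit in Table 5, week 24).

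- Gap per patient: 30 − 5 = 25 days.
- Over the planned sample: 20 × 25 = 500 patient-days at most, if every patient can be observed for 30 days after the last dose.
- Share of the longer window lost under section 4 = 25 / (treatment days + 30):
  - 28 days of treatment: windows of 33 and 58 days; 25/58 = 43%.
  - 168 days of treatment: windows of 173 and 198 days; 25/198 = 13%.

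These are shares of calendar time, not of events.

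**4. Laboratory rule.** Take an abnormality that meets the AE definition and that the investigator judges clinically significant.

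- Grade 4: an SAE under section 4.3.4, so recorded under either rule.
- Below Grade 4 but meeting another SAE criterion, or causing discontinuation: recorded under either rule.
- Below Grade 4, non-serious, patient stays in the study: section 4.3 says it will be recorded; section 3.3.3.2 and footnote b say it should not be, unless the investigator insists.

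Only the third case conflicts. It can matter: in Table 7, the row for other toxicity manages a prolonged or clinically significant Grade 2 event by holding the drug and then reducing the dose. A laboratory toxicity could therefore change a patient's dose and still, by default, not count as an adverse event.

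**The case against.** The strongest reply is that section 4 sets a minimum. It requires recording to day 5 and does not forbid it afterwards, so collecting to day 30 satisfies every section. That is correct, and it is why the repair is simple. It does not remove the problem, because a site following section 4 alone would breach section 3.3.3.2 and footnote e.

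On laboratory findings, the reply is that both rules leave room for the investigator's judgement, so they can largely be applied together. This stands in part. A reader might infer that a non-serious Grade 3 laboratory abnormality could never enter the adverse-event data under footnote b. The documents do not support that, because the investigator may insist. The defaults still differ: under section 4.3 a judgement of clinical significance, together with the AE definition, leads to recording; under footnote b that judgement is not mentioned.

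A reader might also infer that laboratory data are lost. They are not. Table 5 schedules chemistry and haematology at every visit from V2 to V8, and section 3.3.3.2 requires new or worsening Grade 3 or 4 values at discontinuation to be retested and entered on the CRF. What is at risk is whether they are classified as adverse events.

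Two further inferences should be resisted. The hepatic failure and jaundice listed among related deaths in the introduction do not show what would be missed: fatal events are SAEs, captured under either laboratory rule and reported to 30 days. And the 8-week median treatment duration in section 1.3.3.2 would give 25/86 = 29%, but it comes from four earlier studies, two of them in bladder and colorectal cancer, so it is no basis for a single figure here.

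**Conclusion.** The point holds as a contradiction in data collection, in two parts. The adverse-event window differs by 25 days per patient for non-serious events with onset on days 6 to 30. That is about 43% of the longer window after 28 days of treatment and 13% after 24 weeks, assuming those durations and full observation for 30 days. The number of events this represents cannot be derived from the protocol, and off-drug days need not carry the same event rate as days on treatment. The laboratory conflict is confined to non-serious abnormalities below Grade 4 that do not lead to discontinuation.

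The protocol should be corrected because safety is a secondary outcome and the repair is cheap. Serious-event collection to 30 days, the sample size and the primary CTC outcome are unaffected.

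**What to change.** 1. In section 4, change the end of adverse-event recording from *five days* to *30 calendar days* after the last dose. This agrees with section 3.3.3.2, Table 5 footnote e and section 4.4.
2. Reconcile Table 5 footnote b and section 3.3.3.2 with section 4.3 into one laboratory rule, stated the same way in all three places. One way is to add *or is judged clinically significant* to the listed exceptions.

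The cost is a few wording changes and slightly more recorded adverse events. No new follow-up is created, since section 3.3.3.2 already requires the 30 days.
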